### Research questions and hypotheses

#### Primary research question (RQ) and hypothesis

Is two weeks of twice-daily PA treatment more effective in reducing pain and CRPS symptom severity than an identical regime using sham prism adaptation (“sham treatment”)?

Sham prism adaptation has an identical procedure to PA treatment, except that pointing movements are performed without any optical deviation and therefore no adaptation takes place. This will allow us to dissociate the effects of the additional movement of the affected limb imposed by the treatment, to isolate the true effects of PA.

Hypothesis: There will be greater reductions in pain and CRPS symptom severity in the participants who receive PA treatment compared to the participants who receive sham treatment.

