#### Primary outcomes

A change between RS2 (immediately before the commencement of treatment) and RS3 (immediately after the end of the treatment period) in current self-reported pain intensity and CRPS severity score [35, 52] are the primary outcomes. People with CRPS consider pain relief to be the highest priority for recovery [59], and pain intensity is the most common primary outcome in chronic pain trials [60]. Current pain intensity is measured using item 6 of the Brief Pain Inventory (BPI; short form) [42], which is a Numerical Rating Scale (NRS) ranging from 0 – “no pain” to 10 – “pain as bad as you can imagine”. The BPI has high reliability [42]. In addition to pain, CRPS involves a range of other debilitating symptoms, some of which were also affected by PA in previous studies [22, 24]. Therefore, we included a comprehensive measure of symptoms severity as the second primary outcome. The CRPS severity score assessment protocol follows the 16-points scoring system published by Harden and colleagues [35]. This continuous index of CRPS symptom severity has good discrimination abilities, concurrent validity and adequate sensitivity to change [35, 52], and has been recommended as one of the core outcome measures for CRPS clinical studies [61].

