#### Timing

No interim analyses are planned. The timing of the final analyses will be stratified by planned length of follow-up for the relevant outcome measures. Once all participants have completed RS4, we will analyse the RS1-RS4 data to address our research questions regarding the efficacy of PA treatment in reducing CRPS symptom severity (RQ1) and the relationships between the severity of clinical symptoms of CRPS and neuropsychological changes in perception of and attention to the affected limb and its corresponding side of space in RS1 (RQ5). We will conduct separate analyses of current self-reported pain intensity, the BPI, the Pain Detect Questionnaire, the BPDS, the Tampa Scale for Kinesiophobia, the Profile of Mood States, and the Patient’s Global Impression of Change scores once all participants meet the secondary endpoint (LTFU2). Recruitment will be terminated if we are not able to collect 42 full datasets for RS1-RS4 by 1 March 2019.

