#### Efficacy of PA treatment in reducing pain and CRPS symptom severity (RQ1)

A 2 × 6 ANOVA with Group as a between-subjects factor (PA treatment, sham treatment), and Time (RS1, RS2, RS3, RS4, LTFU1, LTFU2) as a within-subject factor will be conducted for the first primary outcome of pain intensity rating. We will also conduct sixteen a-priori contrasts to compare RS1 vs. RS2, RS2 vs. RS3, RS3 vs. RS4, RS2 vs. RS4, RS2 vs. LTFU1, RS4 vs. LTFU1, LTFU1 vs. LTFU2, and RS2 vs. LTFU2 within each group. We will also conduct a 2 × 4 ANOVA with the factors Group (PA treatment, sham treatment) and Time (RS1, RS2, RS3, RS4) for the second primary outcome of CPRS severity score, followed by eight a-priori contrasts comparing RS1 vs. RS2, RS2 vs. RS3, RS3 vs. RS4, and RS2 vs. RS4 within each group. We are primarily interested in detecting any changes between RS2 and RS3 which would represent immediate effects of treatment.

Minimisation factors (see Table 2) may be included as covariates in the ANOVAs if there are significant differences at RS1. Similarly, if we find significant group differences in the Profile of Mood States, Tampa Scale for Kinesiophobia, or Revised Life Orientation Test RS1 scores, these variables may be used as covariates in the ANOVAs on pain and CRPS severity score.

We will also calculate the Number Needed to Treat (NNT) separately for pain and CRPS severity score. The NNT will be based on the proportion of participants in each treatment arm that achieved clinically significant pain relief (≥2 points on 0–10 NRS scale [110]) and reduction in CRPS symptom severity (≥4.9 points [35]) in RS3 compared to RS2.

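### The listed primary contrasts are all within arms; the arms' RS2-to-RS3 changes are compared only through an omnibus Group × Time interaction that is not specific to that interval

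*Protocol article*

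**What the plan says.** The hypothesis, under the primary research question, compares the arms: "There will be greater reductions in pain and CRPS symptom severity in the participants who receive PA treatment compared to the participants who receive sham". The Primary outcomes section fixes the interval for both outcomes: "A change between RS2 (immediately before the commencement of treatment) and RS3 (immediately after the end of the treatment period"), and the Design section makes RS3 the primary endpoint.

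For pain, the RQ1 analysis section plans "A 2 × 6 ANOVA with Group as a between-subjects factor (PA treatment, sham treatment") and Time over all six visits. It then lists eight visit pairs in each arm, ending "RS4 vs. LTFU1, LTFU1 vs. LTFU2, and RS2 vs. LTFU2 within each group". For CRPS severity it plans a 2 × 4 ANOVA with "eight a-priori contrasts comparing RS1 vs. RS2, RS2 vs. RS3, RS3 vs. RS4, and RS2 vs. RS4 within each group". It adds: "We are primarily interested in detecting any changes between RS2 and RS3 which would represent immediate effects of treatment".

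Two other sections bear on this. The general Statistical analyses section says that significant interactions will be followed by contrasts, without saying which, and applies Holm-Bonferroni within each outcome analysis. The Timing section says: "Once all participants have completed RS4, we will analyse the RS1-RS4 data to address our research questions regarding the efficacy of PA treatment". It then schedules a separate analysis of current pain once LTFU2 is complete.

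**The concern.** The question is comparative, but every contrast the plan spells out asks whether one arm changed over time. RS2 versus RS3, the comparison of main interest, appears only in that form. A significant change in PA and a non-significant one in sham do not show that the arms differ. Shared improvement is plausible here, because both arms perform the same arm movements and the sham is there to separate out that effect.

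The Group × Time interaction does compare the arms, but over all visits at once. For pain these include pre-treatment RS1 and the 3- and 6-month postal follow-ups. A significant result need not come from RS2 to RS3, and no between-arm contrast is named to locate it. The article says PA should be developed as a recommended method if it outperforms sham on the primary outcomes, so the test behind that conclusion should be explicit.

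**Working it through.** **Inputs.** From the sample size section: difference 2 points, SD 1.98 (of pain ratings), 5% type I error, 90% power, 21 per arm. The correlation r between visits is not given, so 0.3, 0.5 and 0.7 are assumed. The SD of change is 1.98 × √(2(1−r)), which is 2.343, 1.98 and 1.534 respectively. It equals 1.98 only at r = 0.5.

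**1. Contrast count.** Pain: 8 visit pairs × 2 arms = 16. Severity: 4 × 2 = 8. None is between arms.

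**2. The plan's own sample size.** For a two-sided comparison of two arms, n per arm = 2 × (1.960 + 1.282)² × 1.98² / 2² = 20.6, so 21 per arm and 42 in total, as stated. A within-arm paired test with the same SD needs (1.98 × 3.242 / 2)² = 10.3, so 11 (13 with the t distribution). The stated size is therefore that of a between-arm comparison, which the contrast list omits.

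**3. Side-by-side reading.** Let both arms truly improve by 1.0 point, n = 21 each, with p the power of the paired t-test. The chance that PA is significant and sham is not is p(1−p).

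| r | p at .05 | PA only | p at .05/16 | PA only |
|---|---|---|---|---|
| 0.3 | 0.461 | 25% | 0.114 | 10% |
| 0.5 | 0.596 | 24% | 0.188 | 15% |
| 0.7 | 0.811 | 15% | 0.386 | 24% |

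The .05/16 columns are the strictest Holm step. A two-sided 5% between-arm test would wrongly favour PA 2.5% of the time.

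**4. The same pattern with a significant 2 × 6 interaction also required.** Simulated with the Greenhouse-Geisser correction and equal improvement from RS3 onward: about 0.5–1.6% across the correlation structures tried. If the arms also diverge at late follow-up: about 5–21%.

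**5. Specificity of the interaction for pain.** Under equal correlation between visits, the noncentrality is (n/2) × Σ(d − mean d)² / (σ²(1−r)), where d is the arm difference at each visit. With d = 0 through RS4 and 1.5 at LTFU1 and LTFU2, mean d = 0.5 and the sum is 4 × 0.25 + 2 × 1.0 = 3. At r = 0.5 this gives 10.5 × 3 / (3.92 × 0.5) = 16.1, and 88% power on 5 and 200 df. Simulations gave 87–88% under this structure and 61–80% under decaying correlation with Greenhouse-Geisser. The direct RS2-to-RS3 between-arm contrast stayed at about 5%.

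**6. Power is not the problem.** For a 2-point difference at RS3 only, the 2 × 6 interaction has 78%, 92% and 99% power at r = 0.3, 0.5 and 0.7. The direct contrast has 77%, 89% and 98%.

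**The case against.** The strongest reply is that the plan does compare the arms. Each primary outcome has a Group × Time ANOVA, and the section on secondary outcomes describes the same ANOVAs as a way to analyse between-group differences. Significant interactions get follow-up contrasts, which are not restricted to within-arm ones and may be detailed in an analysis plan that is not shown. The NNT also compares responder proportions between arms over exactly RS2 to RS3. A mixed ANOVA is a legitimate model for this design. A late-only effect runs against the protocol's own expectation that participants return to baseline over time.

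Much of this stands. A reader might infer that the plan has no between-arm test, or that it would declare PA effective when both arms improve equally. The documents support neither. The interaction is a between-arm test, and no stated rule makes success depend on PA being significant and sham not. The 24% describes a misreading that the plan leaves open, not its error rate.

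A reader might also infer that the Timing section contradicts itself on pain. It does not, because it declares a separate pain analysis after LTFU2.

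What does not stand is that these elements supply the missing test. The follow-up contrasts are unspecified and conditional on the omnibus result. The NNT has no stated test. The RQ1 section gives a complete, numbered contrast list that leaves out the one contrast answering the hypothesis, so this is more than detail deferred to another document.

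**Conclusion.** The point holds as a mismatch between the primary hypothesis and the tests specified for it. The hypothesis concerns the arm difference in RS2-to-RS3 change. The listed contrasts are all within an arm, and the between-arm test that exists is an omnibus over four or six visits, not designated as primary.

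For pain, that omnibus can be significant in roughly 60–90% of simulated trials with no arm difference in RS2-to-RS3 change, given a 1.5-point difference at late follow-up only. Side-by-side reading misleads in about 24% of trials under an equal 1-point improvement (about 15% at r = 0.7), but in about 1–2% if a significant interaction is also required and the arms do not diverge later. These figures rest on assumed correlations and assumed effect patterns, with 1.98 as the SD at each visit. None was computed for CRPS severity, whose 2 × 4 model contains no postal follow-up.

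A smaller gap follows from Timing: RQ1 is to be analysed on RS1–RS4 data after the last RS4, but the only pain model given needs LTFU1 and LTFU2.

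**What to change.** For each primary outcome, name one primary test: the PA-minus-sham difference in RS2-to-RS3 change, with its 95% CI. It can be the Group × (RS2, RS3) contrast, or RS3 compared between arms with adjustment for RS2. State that it is run on RS1–RS4 data once the last RS4 is complete, which also supplies the missing pain model for that time point. Keep the 2 × 4 and 2 × 6 ANOVAs and the within-arm contrasts as secondary or descriptive, mainly for RQ3.

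This changes wording only. It needs no new data, and 21 per arm still gives about 89% power for a 2-point difference if the SD of change is 1.98. The cost is that within-arm results can no longer serve as the primary result.

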### Randomisation

Treatment allocation is conducted by method of randomisation with stratification to minimise baseline (RS1) group differences. Eligible participants with CRPS are allocated in equal numbers to one of the two treatment groups: PA treatment group or sham treatment group. Group allocation is performed using MINIM computer programme [34] by a researcher who is not involved in data collection ([name]). The minimisation procedure controls for the stratification factors that are listed in Table 2. In the event of participant’s withdrawal after treatment allocation, but before RS3, their data shall be removed from the minimisation procedure and an additional participant shall be recruited for the trial to ensure equal numbers of full datasets with any post-intervention data in the two groups.

**Table 2 Tab2:** Criteria for stratification as recorded in RS1

Factor	Weight	Categories
Current pain intensity (0–10 Numerical Rating Scale)	2	≤ 6
		> 6
CRPS severity score (1–16) [35]	2	≤ 12
		> 12
Primarily affected arm	1	Left
		Right
Pre-CRPS dominant hand (writing)	1	Left
		Right
Sex	1	Male
		Female
Age	1	18 - < 40
		40 - < 61
		61–80
Presence of CRPS in body parts other than the primary affected arm	1	Yes
		No
Presence of other non-CRPS pain	1	Yes
		No
CRPS duration	1	< 1 year
		1 - < 5 years
		5 - < 10 years
		≥ 10 years

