The Revised Life Orientation Test [48] assesses levels of optimism and pessimism. Participants rate to what extent they agree with 10 statements on a scale from 0 – “strongly disagree” to 4 – “strongly agree”. The Patient Centred Outcomes Questionnaire [49] is also administered to measure patient-centred expectations and criteria for success in chronic pain treatment. Rating scales from 0 to 10 are used to indicate the usual, desired, expected and considered successful levels of pain, fatigue, emotional distress, and interference with daily activities (0 – “none”, 10 – “worst imaginable”), and the importance of improvement in each of these areas (0 – “not at all important”, 10 – “most important”). The decision to include the Revised Life Orientation Test and the Patient Centred Outcomes Questionnaire in the current trial was driven by the fact that optimism and expectations of outcome have been known to influence the success of novel treatments [70–72]. Thus, it is important to confirm that the two treatment groups are matched on these extraneous factors, or to include these variables as covariates in the analysis of outcome measures if they are not.

The participants keep daily logbooks for weeks 1–11 in which they use 0–10 NRSs to record their average level (over the preceding 24 h) of pain (0 – “no pain at all”, 10 – “pain as bad as it could be”), the range of movement in the affected arm (0 – “no movement at all”, 10 – “normal movement”), and the degree to which their symptoms have interfered with their daily life (0 – “no interference at all”, 10 – “complete interference”). These measures are designed to track the time-course of any change in pain, movement, and interference during the first 10 weeks of the study (i.e. four-week baseline period, two-week treatment period, and four-week immediate post-treatment period).

Finally, the Patient Global Impression of Change questionnaire [50] is administered to measure participants’ impression of how much their symptoms have changed due to treatment. It produces a single rating on a scale from 1 – “no change” to 7 – “a great deal better”. The Patient Global Impression of Change is a widely recommended measure of perceived global improvement and satisfaction with treatment [60, 62].

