#### Sample size and power calculation

The required sample size was calculated based on the primary outcome measure of self-reported pain [109]. A meta-analysis defined a clinically significant reduction in pain as a change of Δ = − 2 (on a scale of 0–10) [110]. The sample size required to detect a pain reduction of this magnitude between RS2 and RS3 was estimated. The risk of type I error was set at 5% and the risk of type II error was set at 10%, giving 90% power to detect a significant change in the pain. The standard deviation expected in the current study was estimated as 1.98 based on pain intensity ratings obtained by our group in recent research [8]. Given these parameters, a minimum of 42 participants with CRPS (21 per group) is required to evaluate the effects of the PA treatment on the primary outcome measure of pain. Taking into account an anticipated drop-out rate of 20%, up to 52 participants with CRPS will be enrolled in order to obtain a total of at least 21 complete datasets for RS1-RS4 per treatment group. To provide normative data, 21 healthy (pain-free) control participants will be recruited.

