#### Descriptive characteristics

We will report baseline characteristics for individual participants with CRPS such as affected limb, type of inciting injury, CRPS duration, co-morbidities, prescribed medications and other treatments, and change in handedness score.

Minimisation factors listed in Table 2 will be presented as group means for continuous factors or proportion of participants in each group who are classed positive on each categorical factor. We will conduct a series of contrasts and chi-square tests to confirm that the minimisation procedure successfully equated the two groups on these factors. Contrasts will also be used to confirm that the PA and sham treatment groups are matched on mean Profile of Mood States, Tampa Scale for Kinesiophobia, Revised Life Orientation Test, and Patient Centred Outcomes Questionnaire scores.

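### Primary-analysis covariates are optional and picked by RS1 significance tests after minimisation; prespecifying an RS3 ANCOVA would fix the model and gain precision

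*Protocol article*

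**What the plan says.** The RQ1 efficacy section of the protocol article gives the covariate rule for the primary ANOVAs: "Minimisation factors (see Table 2) may be included as covariates in the ANOVAs if there are significant differences at RS1". The next sentence makes three questionnaires optional covariates in the same way, "if we find significant group differences in the Profile of Mood States, Tampa Scale for Kinesiophobia, or Revised Life Orientation Test RS1 scores".

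The Randomisation section says that "The minimisation procedure controls for the stratification factors that are listed in Table 2". Table 2 lists nine factors. RS1 pain and RS1 CRPS severity score have weight 2 and the other seven weight 1. The Descriptive characteristics section then plans contrasts and chi-square tests "to confirm that the minimisation procedure successfully equated the two groups on these factors".

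The Self-report questionnaires section gives a further rule for optimism and treatment expectations: check that the arms match, "or to include these variables as covariates in the analysis of outcome measures if they are not". Expectations (Patient Centred Outcomes Questionnaire) do not appear in the RQ1 list.

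The Primary outcomes section defines both outcomes as the change from RS2 to RS3. In the pain ANOVA the baseline sessions enter through "Time (RS1, RS2, RS3, RS4, LTFU1, LTFU2) as a within-subject factor"; the severity ANOVA does the same with RS1 to RS4.

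**The concern.** A covariate earns its place by predicting the outcome, and that can be decided before data are seen. Here it is decided by whether the arms happen to differ at RS1. Three things follow.

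- The trigger works against the design. Minimisation suppresses differences on the very factors that are then tested, most of all on RS1 pain and severity.
- The wording is permissive, so even a significant difference does not settle which model is primary. The sections also disagree on whether expectations are a candidate.
- If the trigger did fire for RS1 pain or severity, that score would be both a covariate and a level of the outcome's own Time factor.

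At stake are the precision of the RS2 to RS3 comparison and a primary model that can be named before unblinding.

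**Working it through.** **Inputs from the protocol.** Difference 2 points; SD 1.98; type I error 5%; power 90%; 21 per group. The Sample size section states that "The standard deviation expected in the current study was estimated as 1.98 based on pain intensity ratings obtained by our group", without saying whether this is the SD of a rating or of a change. Two-sided testing is assumed.

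**The plan's own figure.** n per arm = 2 × (1.960 + 1.282)² × 1.98² / 2² = 20.6, rounded up to 21, so 42 in total. This reproduces. Power at 21 per arm is 0.905 by the normal approximation and 0.891 by the noncentral t.

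**How often the trigger fires.** Minimisation was simulated with the Table 2 factors and weights, N = 42 and 1,500 runs. Category frequencies, mean pain 6, mean severity 12 and severity SD 2 are assumptions. The first figure is for deterministic assignment, the second for an assignment probability of 0.8.

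- RS1 pain significant: 0.3% to 0.9% of trials.
- RS1 severity significant: 0.1% to 0.3%.
- At least one of the nine factors: 4.1% to 12.9%.
- Adding the three questionnaires in the RQ1 section as independent 5% tests: 1 − (1 − 0.041) × 0.95³ = 0.18, up to 1 − (1 − 0.129) × 0.95³ = 0.25.

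**Precision.** Let r be the RS2–RS3 correlation, with equal SD s at both sessions.

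- SD of change = s√(2(1 − r))
- ANCOVA residual SD = s√(1 − r²)
- Variance ratio, ANCOVA to change = (1 − r²)/(2(1 − r)) = (1 + r)/2

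With s = 1.98 read as the SD of a rating, 21 per arm and a 2-point between-group difference, noncentral-t power is as follows. The change score has 40 df. ANCOVA has 39 df, with its variance multiplied by 1 + 1/38 for chance imbalance in the covariate.

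| r (assumed) | SD change | SD ANCOVA | Variance ratio | Power, change | Power, ANCOVA |
|---|---|---|---|---|---|
| 0.3 | 2.34 | 1.89 | 0.65 | 77% | 91% |
| 0.5 | 1.98 | 1.71 | 0.75 | 89% | 95% |
| 0.7 | 1.53 | 1.41 | 0.85 | 98% | 99% |
| 0.9 | 0.89 | 0.86 | 0.95 | >99.9% | >99.9% |

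If 1.98 is already the SD of a change, the ANCOVA residual SD is 1.98√((1 + r)/2). By the normal approximation 90% power then needs 14, 16, 18 and 20 per arm at r = 0.3, 0.5, 0.7 and 0.9, against 21.

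**What the planned rule recovers.** A second simulation (21 per arm, complete randomisation, 4,000 runs per scenario) compared an unadjusted change score, adjustment for RS1 only when RS1 differs significantly, and prespecified ANCOVA on RS2.

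- r = 0.5: power 0.899, 0.896 and 0.960; mean standard error 0.608, 0.610 and 0.533.
- r = 0.7: power 0.983, 0.983 and 0.991.
- No true difference: rejection rates between 0.045 and 0.058 for all three.

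The conditional rule therefore performs like no adjustment at all.

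**The case against.** The strongest reply is that the baseline outcome is not discarded. RS1 and RS2 are levels of Time and the primary contrast runs from RS2 to RS3, so the most likely strong predictor is in every primary analysis. That stands. A reader might infer that the best prognostic information goes unused; the documents do not support this. The loss is only that of a change score against ANCOVA, and it is small if r is high.

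A reader might also infer inflated false positives from testing first and adjusting afterwards. The simulation does not show it: rejection rates stayed near 5%, and the highest value, 0.0575, also occurred with the unadjusted change score.

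Nor do the figures show that 42 participants are too few. The stated size reproduces from its inputs, and the 77% applies only if 1.98 is the SD of a rating and r is about 0.3.

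Two further limits are fair. The power figures describe a two-sample comparison of change, whereas the plan names an omnibus Group by Time ANOVA with contrasts within each group, so they are a benchmark and not the plan's own power. And stable effects of age, sex, side or duration largely cancel in a within-participant change; the documents give nothing from which to quantify any remaining loss from omitting those factors.

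One might say that covariates belong in an analysis plan that is not shown. But the article does not leave them open: it states a rule, and that rule is the problem.

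**Conclusion.** The point holds as one of precision and prespecification. The primary model depends on RS1 tests and on discretion, and RS1 pain and severity would become covariates in under 1% of simulated trials. The RS2 to RS3 comparison is in effect an unadjusted change score. ANCOVA on RS2 would cut its variance by 35% at r = 0.3, 25% at 0.5, 15% at 0.7 and 5% at 0.9.

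In power terms the gain matters at r of 0.3 to 0.5 and is slight from 0.7 upwards. This rests on an assumed r, equal variances at RS2 and RS3, and 1.98 being the SD of a rating. The trigger rates also rest on assumed factor frequencies. The direction of the gain depends on none of the assumed values, apart from a small cost in degrees of freedom. It is worth changing, but it does not invalidate the trial.

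**What to change.** - For each primary outcome, name one primary between-group test: RS3 value on group, adjusted for the RS2 value of that outcome and a short fixed list of minimisation factors. The list should hold at least RS1 pain and RS1 CRPS severity, both continuous. Fit it whatever the baseline tests show. RS1 and RS2 of the same outcome then both enter, which uses both baseline visits.
- Remove RS1 significance as a trigger for any covariate.
- Use mood, kinesiophobia, optimism and expectations descriptively or in a named sensitivity analysis, with the same list in every section.
- Keep the 2 × 6 and 2 × 4 ANOVAs as supportive time-course analyses.
- State whether 1.98 is the SD of a rating or of a change.

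Cost: no new data and 2–3 degrees of freedom (three covariates leave 37 of 40). With 42 participants and nine factors the list must stay short. The change replaces the primary test, so it should be recorded and dated before the outcome assessor is unblinded after the last RS4.
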